### 8.5 Definition of patient data to be gathered and directly entered in the patient electronic case file, which will be considered the source data:

#### Inclusion/Randomization visit (M0)

- Consultation date
- Demographic data: date of birth, sex
- History of MN
- Paraclinic tests to eliminate secondary MN when performed: body scan, anti-nuclear antibodies, HBV, HCV serologies
- Current treatment
- Clinical examination: weight, height, blood pressure, edema
- Blood sample: urea, creatinine, electrolytes (Na, K, Cl, HCO3), protein, albumin, full blood count
- Urine collection on a spot morning sample: protein, albumin, urea, creatinine
- Centralized assays : for both groups,

- 2 dry tubes of 5 ml of blood and 2 EDTA tubes of 3 ml of blood will be shipped to Nice at room temperature for PLA2R1-Ab, epitope profile determination, anti-rituximab antibodies, B and T cells counts (see manual lab),
  - 1 lithium heparin tube of 4 ml of blood for cytokine profile analysis will be shipped to Nice at 4°C.
- 
- Start vaccination (pneumococcal and influenza vaccine) between randomization and first injection at the latest.
  - In the GEMRITUX arm, plan M3 in 3 months +/-15days and hand out a prescription to the patient for blood and urine analyses\* (results needed for the next visit as per routine follow-up);
  - In the Personalized Treatment arm, plan next visit according to the epitope profile results provided by the central lab within 48 hours:
    - Restricted anti-CysR activity: 6-month symptomatic treatment as in GEMRITUX arm - > plan M3 visit in 3 months +/-15 days and hand out a prescription to the patient for blood and urine analyses\* (results needed for the next visit as per routine follow-up);
    - Anti-CTLD1/7 activity: plan two 1g rituximab infusions at 2-week interval +/-2 days. The treatment should start between 5 and 14 days after randomization. After the first injection, plan M3 visit in 3 months +/-15 days and hand out a prescription to the patient for blood and urine analyses\* (results needed for the next visit as per routine follow-up)

\* Blood sample: urea, creatinine, electrolytes (sodium, potassium, chloride, bicarbonate), protein, albumin, full blood count.

Spot morning urine sample: protein, albumin, urea, creatinine.

### **M3 visit = 3 months after +/-15 days**

- Consultation date
- Clinical examination: weight, blood pressure, edema
- Serious adverse events
- Changes in concomitant treatments
- Blood and urine lab results

- Centralized assays for both arms:
  - 2 dry tubes of 5 ml of blood and 2 EDTA tubes of 3 ml of blood will be sent to Nice at room temperature for PLA2R1-Ab, epitope profile determination, rituximab serum levels, anti-rituximab antibodies, and B and T cells counts (see manual lab)
- Plan M6 visit +/-15 days and hand out a prescription to the patient for blood and urine analyses\*

\* Blood sample: urea, creatinine, electrolytes (sodium, potassium, chloride, bicarbonate), protein, albumin, full blood count.

Spot morning urine sample: protein, albumin, urea, creatinine.

#### **M6 visit = 6 months after randomization +/-15 days**

- Consultation date
- Clinical examination: weight, blood pressure, edema
- Serious adverse events
- Changes in concomitant treatments
- Blood and urine lab results
- Estimated GFR CKD EPI
- Centralized assays for both arms:
  - 2 dry tubes of 5 ml of blood and 2 EDTA tubes of 3 ml of blood will be shipped to Nice at room temperature for PLA2R1-Ab, epitope profile determination, serum rituximab levels, anti-rituximab antibodies, and, B and T cells counts (see manual lab)
- **In the GEMRITUX arm**
  - If disease still active (UPCR remains > 3.5 g/g and albuminemia < 30 g/l): plan two 375 mg/m^2 Rituximab infusions at 1-week interval (+/- 2 days) between 5 and 14 days after M6 visit.
  - If remission (partial or complete, see p.12): symptomatic treatment to be continued.
- **In the personalized arm/ Patients who received RTX at M0**
  - If remission (partial or complete, see p.12): symptomatic treatment to be continued alone and contraception will be required during 12 months after the end of the treatment.
  - If disease still active / Restricted anti-CysR activity: plan two 375 mg/m^2 rituximab infusions at 1-week interval (+/- 2 days) between 5 and 14 days after M6 visit.

- if disease still active / Anti-CTLD1/7 activity: plan two 1g rituximab infusions at 2-week interval (+/- 2 days) between 5 and 14 days after M6 visit. For patient who will develop anti-rituximab antibodies, treatment with human anti-CD20 is widely recommended.

*NB: If the patient still active disease / anti-PLA2R1 Ab-; the symptomatic treatment should be optimized*

- **In the personalized arm/ Patients who received 6-month symptomatic treatment**

- If remission (partial or complete, see p.12): symptomatic treatment to be continued
- If disease still active / Restricted anti-CysR activity: plan two 375 mg/m^2 rituximab infusions at 1-week interval between 5 and 14 days after M6 visit.
- if disease still active / Anti-CTLD1/7 activity: plan two 1g rituximab infusions at 2-week interval between 5 and 14 days after M6 visit.

**For all:** plan M9 +/-15 days and hand out a prescription to the patient for blood and urine analyses\*

\* Blood sample: urea, creatinine, electrolytes (sodium, potassium, chloride, bicarbonate), protein, albumin, full blood count.

Spot morning urine sample: protein, albumin, urea, creatinine.

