## 2. Study objectives

### 2.1 Primary objective

Our main objective is to compare the efficacy of a **personalized treatment** of nephrotic iMN driven by anti-PLA2R1 antibody epitope profile at month 0 and month 6 to induce clinical remission (partial or complete) of the nephrotic syndrome at month 12:

- Restricted anti-CysR activity at month 0: 6-month symptomatic treatment
- Restricted anti-CysR activity at month 6 after symptomatic treatment and if the nephrotic syndrome persists at month-6 (UPCR remains  $> 3.5$  g/g and albuminemia  $< 30$  g/l): two 375 mg/m^2 rituximab infusions at 1-week interval

- Anti-CTLD1/7 activity at month 0 or month 6: two 1g rituximab infusions at 2-week interval at month 0 and/or month 6

with the GEMRITUX protocol: 6 months of symptomatic antihypertensive and antiproteinuric therapy, and if the nephrotic syndrome persists at month-6 (UPCR remains > 3.5 g/g and albuminemia < 30 g/l), two 375 mg/m^2 infusions at 1-week interval. For patients who will develop anti-rituximab antibodies, treatment with human anti-CD20 is widely recommended.

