## 3. Evaluation criteria

### Principal evaluation criteria:

Clinical remission will be defined as a composite criterion combining (KDIGO definitions):

- Complete clinical remission: urinary protein/creatinine ratio (UPCR)<0.3 g/g in spot morning urine samples and Normal serum albumin and eGFR > 60 ml/min/1.73 m^2

- Partial clinical remission: UPCR < 3.5 g/g with a decrease greater than 50% from baseline and improvement or normalization of the serum albumin concentration and increase of serum creatinine lower than 20%

Secondary evaluation criteria:

1. Complete clinical remission as defined above
2. Partial clinical remission as defined above
3. Immunological remission: full PLA2R1 depletion measured by ELISA (titer<14RU/ml)
4. Proteinuria and albuminuria are measured on urine sample (proteinuria-to-creatinine ratio or albuminuria-to-creatinine ratio g/g) or collected during one day (g per day)
5. Change in proteinuria are measured in percentage change in proteinuria from baseline to M6, M9, M12, M18, M24
6. Serum creatinine is measured in blood sample in  $\mu\text{mol/l}$  and eGFR using the CKD-EPI formula.
7. Change in serum creatinine and eGFR are measured in percentage change from baseline to M6, M9, M12, M18, M24
8. PLA2R1-Ab titer are measured by ELISA in RU/ml
9. Severe infections are defined as infections that led to hospitalization during study follow-up
10. Remission will be defined as already stated. Patients from both groups will be analysed jointly. The following risk factors will be studied in this analysis:
  - Lymphocyte counts: B cells (CD19, transitional, mature and memory) and T cells (CD3, CD4, CD8 and TReg) measured in blood sample at J0, M3, M6, post-rituximab infusion
  - Serum level of cytokines (pg/ml) measured in blood sample at J0, and after first remission (or M24 if no remission)
  - Residual serum rituximab levels ( $\mu\text{g/ml}$ ) measured in blood sample at M3 post-rituximab infusion using ELISA
  - Neutralizing anti-rituximab antibodies (ng/ml) measured in blood sample at M3 and M6 post-rituximab infusion
11. Responders are patients entered in partial or complete remission at M12. Relapse is defined by an increased proteinuria > 3.5 g/g after remission at M12. Patients from both groups will be analysed jointly. The risk factors studied will be the same as above measured at J0, M3, M6, M9 and M12 post-rituximab infusion.

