## **6. Selection and exclusion criteria for study participants**

### **6.1 Inclusion criteria**

- Age 18 years or more
- Anti-PLA2R1 activity detected by ELISA or Euroimmune IFA
- Nephrotic syndrome defined by proteinuria > 3.5 g/24h (or UPCR > 3.5 g/g) and serum albumin < 30 g/L at diagnosis
- eGFR (CKD-EPI) > 30 ml/min/1.73 m^2 at diagnosis
- Symptomatic treatment according to KDIGO guidelines: maximal tolerated dose of NIAT (angiotensin-converting enzyme inhibitor and/or angiotensin 2 receptor blockers, diuretics and statins)
- Medical insurance
- Signed informed consent
- Having understood and accepted the need for long-term medical follow-up
- Woman of child-bearing age must be using an effective method of contraception

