## 7. Sample size calculation

### 7.1 Estimate of remission rate in the personalized arm

According to our preliminary data, about 30% of patient with iMN have CysR restricted activity at diagnosis. About 50% will enter in spontaneous remission after 6 months of NIAT and 40% after NIAT + Rituximab at low doses (375 mg/m^2 D0 and D7).

About 70% of patients have CTLD1/7 activity, in our cohorts, about 85% entered in remission after repeated pulses of high doses of rituximab.

We therefore expect a remission rate of 80% at M12 in the personalized arm.

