#### **8.4 Frequency of follow-up visit-protocol**

After randomization, all patients will be scheduled at M3, M6, M9, M12, M18 and M24 post-treatment for a routine follow-up, and benefit from a symptomatic antihypertensive and antiproteinuric treatment throughout the study period according to the KDIGO guidelines.

In the GEMRITUX group: at M6, if the patient exhibits an active disease (UPCR remains  $> 3.5$  g/g and albuminemia  $< 30$  g/l), they will receive two 375 mg/m^2 rituximab infusions at 1-week interval.

In the personalized group, rituximab injections should be scheduled between 5 and 14 days after randomization in case the epitope results are in favor for immunosuppressive treatment, as follows:

- at M0 and M6, if the patient exhibits anti-PLA2R1 anti-CTLD1 or CTLD7 activity, they will receive two 1 g infusions at 2-week interval.
- At M6, if a patient has an active disease/ anti-PLA2R1 ab + or if he has an active disease /anti-PLA2R1 Ab –, symptomatic treatment should be optimized. And if he exhibits anti-CysR restricted activity with active disease (UPCR remains  $> 3.5$  g/g and albuminemia  $< 30$  g/l), they will receive two 375-mg/m^2 rituximab infusions at 1-week interval.

[figure not shown]

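### Entry accepts a 24-hour value or a UPCR, but the month-6 rituximab rule accepts only a UPCR, so a patient with unchanged nephrotic syndrome can fail it

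*Protocol*

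**What the plan says.** Section 6.1, like the Summary, sets the entry condition as "Nephrotic syndrome defined by proteinuria > 3.5 g/24h (or UPCR > 3.5 g/g) and serum albumin < 30 g/L at diagnosis". Either measure of proteinuria is enough.

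At month 6 the condition for rituximab in the GEMRITUX arm is "If disease still active (UPCR remains > 3.5 g/g and albuminemia < 30 g/l"). The same pair of thresholds, without a 24-hour alternative, appears in the Summary, in the GEMRITUX definition under the abbreviations, and in sections 1.3, 2.1 and 8.4. It governs the GEMRITUX arm and the CysR-restricted patients of the personalized arm.

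For patients with CTLD1/7 activity the sections differ. The Summary and section 1.3 attach the UPCR threshold at month 6. Section 2.1 does not: "Anti-CTLD1/7 activity at month 0 or month 6: two 1g rituximab infusions at 2-week interval at month 0 and/or month 6". Section 8.4 also sets none. The month-6 visit says "if disease still active / Anti-CTLD1/7 activity: plan two 1g rituximab infusions at 2-week interval (+/- 2 days") and gives no number for active disease in that arm.

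Section 3 defines partial remission by "UPCR < 3.5 g/g with a decrease greater than 50% from baseline", together with conditions on albumin and creatinine. Its secondary criterion 4 allows proteinuria as a ratio "or collected during one day (g per day"), but nothing links that option to the treatment decision. The urine prescribed for the visits is a spot morning sample.

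**The concern.** The rule is meant to treat patients whose nephrotic syndrome has persisted through six months of symptomatic treatment. Section 8.1 describes that as the point at which immunosuppression starts. Entry and month 6 nevertheless use two definitions of one condition. The month-6 wording speaks of a UPCR that *remains* above 3.5 g/g, which presumes that it was above 3.5 g/g at the start. Entry does not require that.

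A patient admitted on a 24-hour value alone may therefore be as nephrotic at month 6 as at entry and still fall outside the rule. The GEMRITUX arm has two branches at that visit, active disease and remission, and this patient fits neither. What remains is the background care of section 8.4, under which patients "benefit from a symptomatic antihypertensive and antiproteinuric treatment throughout the study period", or withdrawal under section 10.10 if another treatment seems better. Section 9.3 prohibits other immunosuppressive agents. The drug that the strategy intends for persisting disease is withheld because of the unit of measurement.

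**Working it through.** There is no planned figure to reproduce. The check is a unit conversion followed by a comparison of definitions.

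**Inputs.** Let P be 24-hour proteinuria in g and C be 24-hour creatinine excretion in g. The entry threshold is P > 3.5 or UPCR > 3.5 (section 6.1). The month-6 threshold is UPCR > 3.5 with albumin below 30 g/L (month-6 visit). The Protocol gives no value for C, so I assume a range. I also assume that the spot UPCR equals the 24-hour ratio.

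**Formula.** UPCR = P / C. A patient enters on the 24-hour value but fails the month-6 rule while unchanged when 3.5 < P ≤ 3.5 × C. This band is empty unless C exceeds 1.0.

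| C (g/day, assumed) | Upper limit 3.5 × C | Entry values affected (g/24h) |
|---|---|---|
| 1.0 or less | 3.5 or less | none |
| 1.2 | 4.2 | above 3.5, up to 4.2 |
| 1.5 | 5.25 | above 3.5, up to 5.25 |
| 1.8 | 6.3 | above 3.5, up to 6.3 |

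**One case.** P = 5 g/24h and C = 1.5 g/day, with albumin below 30 g/L, all unchanged from entry to month 6:

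1. Entry: 5 > 3.5, so the patient is eligible.
2. Month-6 UPCR: 5 / 1.5 = 3.33 g/g, which is not above 3.5, so the rituximab rule is not met.
3. Partial remission: the UPCR is below 3.5 g/g, but the fall from baseline is 0%, not more than 50%, so it is not met.
4. Complete remission: 3.33 g/g is not below 0.3 g/g, so it is not met.

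The patient is nephrotic by the entry definition, is not in remission, and is not treated.

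**Would using the entry definition at month 6 create an overlap with remission?** A patient who qualified only on the 24-hour value has an entry UPCR of at most 3.5. After a fall of more than 50% the UPCR is below 3.5 × 0.5 = 1.75. The 24-hour value can then exceed 3.5 g only if C is above 3.5 / 1.75 = 2.0 g/day. The overlap is narrow but possible, so the amended rule needs an order of precedence.

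**The case against.** The strongest reply is that no affected patient can be shown from the Protocol. Four things must coincide: entry on a 24-hour value alone, creatinine excretion above 1 g/day, a UPCR of 3.5 g/g or less at month 6, and albumin still below 30 g/L. Spot urine is taken from M0 onwards, which suggests that UPCR was the intended working measure and the 24-hour value was seen as an equivalent at diagnosis. All of this stands as a limit on the weight of the point. It does not repair the rule, which misfires when followed as written.

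It can also be said that the units are only the narrower gap. Patients who improve by less than 50% to a UPCR below 3.5 g/g, or whose albumin reaches 30 g/L, also have no branch of their own at month 6. That is correct.

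A reader might go further and infer a bias in favour of the personalized arm. CTLD1/7 patients in that arm are infused at M0 whatever their UPCR, while such controls must pass the month-6 gate before a first course. The documents do not support that inference:

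- The share of such patients is unknown. CysR-restricted patients face the same gate in both arms, so their contribution cancels in expectation.
- Section 1.3 gives spontaneous remission of CTLD1/7 patients as 0.05% to 17%. The lower figure is 1 in 2,000, which is implausible for the series of 69 and 58 patients in section 1.2.
- For high-dose rituximab, the 64% of section 1.3 is a six-month figure. Section 7.1 says "about 85% entered in remission after repeated pulses of high doses of rituximab". The two differ in time and in number of courses, so their difference does not measure what a second course adds.
- Whether CTLD1/7 patients infused at M0 face a UPCR gate for retreatment depends on reading the GEMRITUX-arm threshold into the personalized-arm lines. Sections 2.1 and 8.4 set no such gate.
- The low-dose course gave 35.1% against 21.1% remission at six months in the earlier trial (section 1.1, p = 0.21). A loss by month 12 from omitting it is not established here.

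**Conclusion.** The inconsistency is in the text, and its logical consequence holds whenever creatinine excretion exceeds 1 g/day: an eligible patient can be unchanged at month 6, be in neither form of remission, and be denied rituximab. The size that can be stated is the width of the band of 24-hour values, from none at 1.0 g/day to 3.5–6.3 g at 1.8 g/day. It rests on assumed creatinine excretion and on a spot ratio equal to the 24-hour ratio. The number of patients affected and the effect on the comparison of the arms, including its direction, cannot be derived. The point is minor. It concerns treating persisting nephrotic syndrome as entry defines it, and is no claim about the primary result.

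**What to change.** In the Summary, the GEMRITUX definition under the abbreviations, sections 1.3, 2.1 and 8.4, and the month-6 visit, let the month-6 criterion read: proteinuria above 3.5 g/24h or UPCR above 3.5 g/g, with albumin below 30 g/L. Add that remission as defined in section 3 takes precedence. Ask for a 24-hour collection at month 6 only from patients who qualified on a 24-hour value.

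An alternative needs no extra collection: a patient whose M0 spot UPCR was 3.5 g/g or less counts as still active at month 6 if albumin is below 30 g/L and section 3 remission is not met. This is somewhat broader, since it also treats such patients when they have improved by less than half.

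The cost is one wording amendment and, under the first option, one home urine collection in that subset. Section 3 already recognises a one-day collection. Eligibility and sample size stay as they are. Neither option gives a branch to patients who entered with a UPCR above 3.5 g/g and improve by less than 50% to below it, or to those whose albumin reaches 30 g/L. A stated action for them could be added in the same amendment.

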**M9 visit = 9 months after randomization +/-15 days**

- Consultation date
- Clinical examination: weight, blood pressure, edema
- Serious adverse events
- Changes in concomitant treatments
- Blood and urine lab results
- Estimated GFR CKD EPI
- Check remission status:
  - Complete clinical remission: urinary protein/creatinine ratio (UPCR) < 0.3 g/g in spot morning urine samples and Normal serum albumin and eGFR > 60 ml/min/1.73 m^2
  - Partial clinical remission: UPCR < 3.5 g/g with a decrease greater than 50% from baseline and improvement or normalization of the serum albumin concentration and increase of serum creatinine lower than 20%
- Centralized assays for both arms:

- 2 dry tubes of 5 ml of blood and 2 EDTA tubes of 3 ml of blood will be sent to Nice at room temperature for PLA2R1-Ab, epitope profile determination, serum rituximab levels, anti-rituximab antibodies, and B and T cells counts (see manual lab)
- Plan visit M12 +/-15 days and hand out a prescription to the patient for blood and urine analyses\*

\* Blood sample: urea, creatinine, electrolytes (sodium, potassium, chloride, bicarbonate), protein, albumin, full blood count.

Spot morning urine sample: protein, albumin, urea, creatinine.

#### **M12 visit = 12 months after randomization +/-15 days**

- Consultation date
- Clinical examination: weight, blood pressure, edema
- Serious adverse events
- Changes in concomitant treatments
- Blood and urine lab results
- Estimated GFR CKD EPI
- Check remission status:
  - Complete clinical remission: urinary protein/creatinine ratio (UPCR) < 0.3 g/g in spot morning urine samples and Normal serum albumin and eGFR > 60 ml/min/1.73 m^2
  - Partial clinical remission: UPCR < 3.5 g/g with a decrease greater than 50% from baseline and improvement or normalization of the serum albumin concentration and increase of serum creatinine lower than 20%
- Centralized assays for both arms:
  - 2 dry tubes of 5 ml of blood and 2 EDTA tubes of 3 ml of blood will be shipped to Nice at room temperature for PLA2R1-Ab, epitope profile determination, serum rituximab levels, anti-rituximab antibodies, B and T cells counts (see manual lab)
- Plan visit M18 +/-15 days and hand out a prescription to the patient for blood and urine analyses\*
- For all patients treated by rituximab, contraception of 12 months will be required after the end of the treatment.

\* Blood sample: urea, creatinine, electrolytes (sodium, potassium, chloride, bicarbonate), protein, albumin, full blood count.

Spot morning urine sample: protein, albumin, urea, creatinine.

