### Schedule of assessments

|                                          | M0 | M3                                | M6 | M9 | M12 | M18 | M24 |
|------------------------------------------|----|-----------------------------------|----|----|-----|-----|-----|
| Selection criteria                       | X  |                                   |    |    |     |     |     |
| Informed Consent                         | X  |                                   |    |    |     |     |     |
| Pregnancy test                           | X  | X                                 | X  | X  | X   |     |     |
| Randomisation                            | X  |                                   |    |    |     |     |     |
| Medical history and demographics         | X  |                                   |    |    |     |     |     |
| Weight, Edema, Blood pressure            | X  | X                                 | X  | X  | X   | X   | X   |
| Vaccination                              | X  |                                   |    |    |     |     |     |
| HBP Medications                          | X  | X                                 | X  | X  | X   | X   | X   |
| Serious adverse events treatment related | X  | X                                 | X  | X  | X   | X   | X   |
| Estimated GFR CKD EPI                    |    |                                   | X  | X  | X   | X   | X   |
| Urine analyses                           | X  | X                                 | X  | X  | X   | X   | X   |
| Blood sample b                | X  | X                                 | X  | X  | X   | X   | X   |
| PLA2R1-Ab                                | X  | X                                 | X  | X  | X   | X   | X   |
| Epitope Profile                          | X  | X                                 | X  | X  | X   | X   | X   |
| Residual Rituximabemia                   |    | X                                 | X  | X  | X   |     |     |
| Rituximab-Ab                             | X  | X                                 | X  | X  | X   |     |     |
| Cytokine profile                         | X  | X At first remission a |    |    |     |     |     |
| B and T cells count                      | X  | X                                 | X  | X  | X   | X   | X   |
| End of study                             |    |                                   |    |    |     |     | X   |

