#### **10.11 Pregnancy**

If a woman becomes pregnant during the course of this study, the patient will be excluded.

All medical decisions concerning her and her fetus will be in Multidisciplinary consultation meeting and will be presented thereafter.

- Reporting of pregnancy

Irrespective of the treatment received by the subject, any pregnancy occurring during the study must be reported immediately.

Pregnancies must be reported on the Sponsor Pregnancy form, which is sent to Sponsor pharmacovigilance (see contact details provided on the pregnancy form), and on the AE page in the e-CRF.

- Follow-up of pregnancy

Any pregnancy must be followed to its conclusion and its outcome must be reported to the Sponsor pharmacovigilance.

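### No pregnancy test is scheduled after M12, although the protocol's own 12-month contraception period runs to about M18.3-M19 for every patient given rituximab after M6

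*Protocol*

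**What the plan says.** The rule on duration is in section 8.5 of the protocol, at the M12 visit: "For all patients treated by rituximab, contraception of 12 months will be required after the end of the treatment". It covers both arms and both regimens.

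The schedule of assessments has a row labelled "Pregnancy test", marked at M0, M3, M6, M9 and M12. The M18 and M24 cells are empty. The visit lists in 8.5 mention no pregnancy test at any visit, so the tests exist only in that table.

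When rituximab is given depends on arm and epitope profile (8.4 and 8.5):

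- **GEMRITUX arm:** only after the M6 visit, and only if disease is still active. The timing is "Rituximab infusions at 1-week interval (+/- 2 days) between 5 and 14 days after M6 visit".
- **Personalized arm, anti-CTLD1/7 activity at M0:** two 1 g infusions two weeks apart (+/-2 days), starting 5-14 days after randomization.
- **Personalized arm at M6, first treatment or retreatment:** either regimen. For the 1 g course after earlier rituximab: "if disease still active / Anti-CTLD1/7 activity: plan two 1g rituximab infusions at 2-week interval (+/- 2 days) between 5 and 14 days after M6 visit".

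The M6 visit text mentions contraception in one branch only, that of personalized-arm patients treated at M0 who are in remission: "symptomatic treatment to be continued alone and contraception will be required during 12 months after the end of the treatment". The M6 branches that lead to infusion, in either arm, do not repeat it.

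Section 6.1 makes effective contraception an entry criterion for women of child-bearing age. Section 10.11 states that "any pregnancy occurring during the study must be reported immediately" and asks for follow-up to the outcome.

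**The concern.** The test calendar appears to be built around treatment at M0. All control-arm rituximab, all first treatment of patients who began on symptomatic therapy, and all retreatment come after M6. For these patients the protocol's post-treatment period extends well past the last scheduled test.

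What is at stake is participant safety. The protocol treats the 12 months after rituximab as a period when pregnancy should be avoided, and it wants any pregnancy reported at once. For patients treated after M6, more than half of that period has no planned test, so a pregnancy would come to light only if the participant noticed and reported it.

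**Working it through.** The protocol gives no figure for this interval, so there is none to reproduce. The check is calendar arithmetic.

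**Inputs, all from the protocol**

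- First infusion: 5 to 14 days after randomization or after the M6 visit (8.4, 8.5).
- Second infusion: 7 +/-2 days later for 375 mg/m², or 14 +/-2 days later for 1 g (8.5). At M6, the branch for personalized-arm patients who had only symptomatic treatment gives no tolerance; the same +/-2 days is assumed.
- Contraception: 12 months from the end of treatment (8.5, M12 visit).
- Last scheduled test: M12 (schedule of assessments).
- Visit windows: +/-15 days at M6 and M12 (8.5). Visits are counted from randomization, as the M6 to M24 headings in 8.5 state.
- 1 month = 30.44 days.

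**Formulas**

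- Last infusion = treatment time point + start delay + infusion interval.
- End of period = last infusion + 12 months.
- Gap = end of period − M12.

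**Days from the treatment time point to the last infusion**

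- 375 mg/m²: 5 + 5 = 10 to 14 + 9 = 23 days, or 0.33 to 0.76 month.
- 1 g: 5 + 12 = 17 to 14 + 16 = 30 days, or 0.56 to 0.99 month.

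**Results at nominal visit dates**

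| Treated | Last infusion | 12 months end | Gap after the M12 test |
|---|---|---|---|
| Controls, 375 mg/m² after M6 | M6.33-M6.76 | M18.33-M18.76 | 6.3-6.8 months |
| Personalized, 375 mg/m² after M6 | M6.33-M6.76 | M18.33-M18.76 | 6.3-6.8 months |
| Personalized, 1 g after M6 | M6.56-M6.99 | M18.56-M18.99 | 6.6-7.0 months |
| Personalized, 1 g at M0 only | M0.56-M0.99 | M12.56-M12.99 | 0.6-1.0 month |

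Across the courses given after M6 the gap is 6.3-7.0 months. As a share of the 12 months this is 6.33/12 = 53% to 6.99/12 = 58%.

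**With the visit windows fully used**

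For courses given after M6, the M6 and M12 windows together move the gap by up to 30 days each way. For the M0 course only the M12 window applies.

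- 375 mg/m² after M6: 6 + (10 − 30)/30.44 = 5.3 to 6 + (23 + 30)/30.44 = 7.7 months.
- 1 g after M6: 6 + (17 − 30)/30.44 = 5.6 to 6 + (30 + 30)/30.44 = 8.0 months.
- 1 g at M0 only: (17 − 15)/30.44 = 0.1 to (30 + 15)/30.44 = 1.5 months.

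**Which existing visits would span the period**

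At nominal dates the period after an M6 course ends 0.3-1.0 month after the M18 visit. A test at M18 alone would leave about that much uncovered, similar to what M0-only patients have now. Of the existing visits, only M24 falls after the end.

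**The case against.** The strongest reply is that nothing in the protocol says scheduled tests must last as long as required contraception. They are separate safeguards, and others remain. The M18 and M24 visits take place with clinical examination and review of serious adverse events, participants are asked about adverse experiences at every visit (10.3), and pregnancies must be reported whatever the treatment (10.11). Contraception is required at entry in both arms (6.1). All of this stands. A reader might infer that the months after M12 are unmonitored; the documents do not support that. What is missing is a scheduled test.

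A reader might also infer from the M6 text that patients infused at M6 first learn of the 12-month rule at M12. The position of a sentence in an investigator document does not show when patients are told, and the consent pages are not in the available copy. What stands is a drafting inconsistency: one M6 branch carries the requirement, while the branches leading to infusion do not.

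Third, the gap might be read as a control-arm problem that biases a comparison. Personalized-arm patients treated after M6 have the same or a slightly longer gap, and pregnancy is not a compared endpoint in sections 2.2, 3 or 12.3.

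Finally, the women affected may be few. That is fair. Counts of all patients treated at M6 would include men and older women, and the protocol gives no number for women of child-bearing age.

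None of this removes the mismatch. The protocol sets a 12-month period and tests repeatedly within it, then stops at a point that suits only those treated at M0.

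**Conclusion.** The point holds as a mismatch between the pregnancy-test schedule and the protocol's own contraception period. For anyone treated after M6, the last 6.3-7.0 months of the 12 (5.3-8.0 with visit windows) have no scheduled test, against 0.6-1.0 month (0.1-1.5) for patients treated only at M0. During that interval detection relies on self-report at continuing visits and on the reporting duty.

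The result rests on the infusion timings in 8.5, on visits counted from randomization, and on the same +/-2 days in the one M6 branch that omits it. It applies only to women of child-bearing age who receive rituximab after M6, whose number is not stated; controls in remission at M6 receive none. The sample size and the primary analysis are unaffected. It is worth correcting because it concerns participant safety and costs little.

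**What to change.** The sponsor should make two sets of passages agree:

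1. The pregnancy-test row in the schedule of assessments and the M18 and M24 visit lists in 8.5, with the post-rituximab contraception period in 8.5. Scheduled testing at the existing M18 and M24 visits would then span that period for women of child-bearing age treated after M6. The visit lists should name the tests, which now appear only in the table.
2. The M6 branches in 8.5 that lead to rituximab, in both arms, with the statement for all treated patients at the M12 visit.

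The length of the contraception period is not questioned, and no other clinical rule is proposed.

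The cost is protocol wording and up to two extra tests per affected woman. M18 and M24 already include blood and urine sampling, so no visit or sample is added.
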